#### Structural integrity

2.14.2

This analysis plan will also be guided by findings from behavioral data using contrasts to evaluate within and between-group differences, along with interaction effects, in structural integrity of specific WM tracts.

#### fNIRS data

2.14.3

HbO and HbR beta values will be used in a mixed effects model to assess prospective within and between-group differences, along with interaction effects, in neural activation over ROIs.

#### Cognition

2.14.4

Standardized scores and T-scores from the List Sorting Working Memory Test, the Flanker Inhibitory Test, and the Dimensional Change Card Sort Test will be used in a mixed effects statistical model to assess prospective within and between-group differences, along with interaction effects, in cognition.

#### Self-reported quality of life

2.14.5

Standardized scores and T-scores from the Traumatic Brain Injury Quality of Life Short Form Measure will be used in a mixed effects statistical model to assess prospective within and between-group differences, along with interaction effects, in self-reported quality of life.

#### Qualitative data

2.14.6

Focus group and interview data are audio-recorded, transcribed verbatim, and de-identified. We will use NVivo software (QSR International Pty Ltd.) to support data analyses. We will use deductive and inductive analytic techniques. Deductively, we will analyze the transcripts for content related to the Consolidated framework for implementation research (CFIR) constructs (Damschroder et al., 2009), with intent to help explain elements of the intervention or study process that can be adapted for a future study. Inductively, we will use open, *in-vivo*, holistic coding (Glaser, 1965; Saldana, 2016). These open codes may be generated based on the participants’ perceptions of the intervention’s impact on their lives and to share how they perceived the intervention overall (e.g., related to ease of attendance, sense of engagement in sessions, etc.).

### Additional statistical analysis plans for all outcomes

2.15

No additional statistical analyses of subgroups are planned at this time. Missing data will be managed with data removal; imputation is not planned.

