### Participant retention

2.4

To support participant retention, during eligibility screening, participants are fully informed of all study components and when each will occur. This is done to prevent loss of data and/or attrition due to known conflicts. Additionally, participants are sent reminders (via text message) for all study appointments, including pre-intervention assessment visits, yoga/exercise class sessions, and post-intervention assessment visits. To further support retention, attendance is taken at each class session, and participants are contacted if they miss a session and their reason for missing is recorded. Additionally, participant incentives are provided at the end of the last yoga/exercise class. Incentives are study materials – exercise mats, smart watches, and chest straps – that are used for each session and retained by the study team, so they are not lost or forgotten for sessions. Post-intervention assessment visits will be completed for all participants who participate in yoga/exercise sessions, but attendance data will be used to interpret post-intervention data, particularly for participants who miss multiple sessions.

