### Sample size

2.5

Power was determined by focusing on the primary outcome of balance. Thus, using balance data from our first feasibility study (Stephens et al., 2020), a power analysis was completed in G Power (version 3.118) (Faul et al., 2007) using a matched pairs t-test with a medium effect size (*d* = 0.5), a minimum power of 0.8 and a significance level of 0.05 to determine that 17 participants per group are needed (*n* = 34). We planned to enroll 48 participants due to potential attrition or enrollment challenges. Limited enrollment was achieved for Cohort 1 so planned enrollment is now 36 participants which still meets the minimum power to detect a medium effect size.

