### Random allocation of intervention arms

2.6

The study biostatistician created the allocation sequence. Up to twenty-four subjects for each cohort were randomly assigned to the yoga or exercise group. First, two blocks of 12 were created, and the randomization scheme was applied separately to each block. Within each block, 12 random numbers were generated using the pseudo-random number generating rand() function in Microsoft Excel. For the first cohort (where 12 individuals were recruited), six of those random numbers were associated with the yoga group and six were associated with the control group. The random number and associated group label were sorted from smallest random number to largest. The resulting randomization scheme was assigned to enrolled participants 001–012 such that six participants were randomly assigned to the yoga group and six participants were randomly assigned to the exercise group for the first cohort. The final allocation sequence was shared with the Co-PI and project manager, who is responsible for creating sealed envelopes that link participant IDs to group assignment. These steps will be repeated for the second cohort. Implementation of group assignment is completed in the following steps. First, the project manager or the PI screens participants for eligibility. Eligible participants are scheduled for a pre-intervention assessment visit where consenting, enrollment, and data acquisition are completed. Following consent, participants are given a unique participant ID number that is given in order of arrival to pre-intervention assessment visits. For example, the first person who arrives for a pre-intervention assessment is given a participant ID of 001. At the end of the pre-intervention visit, the project manager gives participants their sealed envelope, so they are aware of their group assignment.

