#### Primary outcomes

2.9.1

Primary outcome data are acquired at pre-intervention and post-intervention assessments, and measures used to evaluate HRV are acquired throughout both interventions. Pre-intervention assessments are scheduled 2–3 weeks before start of yoga or exercise sessions, and post-intervention assessments are scheduled within 2 weeks of the last yoga or exercise session. See Figure 1 for additional detail on the participant timeline.

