### Consent

3.3

Written informed consent is acquired by the study PI and Co-PI from participants or their legal power of attorney. This study includes two consent forms (see appendices) – one for the main study and one specific to MRI procedures (this is only acquired from participants who are eligible for MRI). Consent is acquired during a pre-intervention assessment visit, which occurs after participants are screened for eligibility. To note, if participants are deemed ineligible for the study during screening, the research team retains none of their information, with the exception of their initial email correspondence for recruitment tracking. Written informed consent procedures include the following steps: (1) Participants are emailed consent form(s) in advance of their pre-intervention assessment visit. (2) Upon arrival at the pre-intervention assessment visit, participants review a printed copy of the consent form(s) with the PI or Co-PI, who clarify procedures and answer questions. (3) After questions are addressed, participants initial and sign consent form(s) and the PI or Co-PI also signs the form(s). All participants are offered a copy of the signed consent form at this time. (4) Throughout the study, participants are reminded that they can decline to complete any procedures, which has no penalty except possible removal from the study.

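### Randomised people who never start a session have no stated post-intervention visit, and the undefined removal rule for missing data may let behaviour after randomisation decide who is analysed

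*Protocol article*

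**What the plan says.** The missing-data rule is one sentence in section 2.15: "Missing data will be managed with data removal; imputation is not planned". It does not say whether the missing value or the whole participant is removed.

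Section 2.4 sets out who is seen at the end: "Post-intervention assessment visits will be completed for all participants who participate in yoga/exercise sessions". The same sentence goes on to say that "attendance data will be used to interpret post-intervention data, particularly for participants who miss multiple sessions". Incomplete attendance therefore does not exclude anyone from the visit, and no minimum attendance is set.

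On timing, section 2.6 states: "At the end of the pre-intervention visit, the project manager gives participants their sealed envelope, so they are aware of their group assignment". Section 2.9.1 adds: "Pre-intervention assessments are scheduled 2–3 weeks before start of yoga or exercise sessions". The post-intervention visit falls up to two weeks after the final class, whereas section 2.4 says that "participant incentives are provided at the end of the last yoga/exercise class".

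Section 2.13 plans mixed effects models with time and group for both primary outcomes. Section 2.5 derives 34 participants "using a matched pairs t-test with a medium effect size" (d = 0.5, power 0.8, significance level 0.05) and says that the reduced target of 36 still meets the minimum power.

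**The concern.** Randomisation makes the arms comparable as allocated. That protection weakens if, after people know their arm, their own behaviour decides whether they are measured and analysed. Here a randomised person has two to three weeks, knowing the allocation, in which to decide not to start. The stated follow-up does not clearly reach that person, and the missing-data rule may then take the person out of the analysis altogether.

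At stake is the yoga-versus-exercise comparison, which is the reason the trial has a control arm and the basis of its autonomic hypothesis. The reduced target also leaves few losses to spare.

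**Working it through.** **1. Path of a randomised non-starter.**
- Baseline visit: measured, then told the arm (section 2.6).
- Next two to three weeks: withdraws before the first class (interval from section 2.9.1).
- Post-intervention visit: promised to people who take part in sessions (section 2.4). This person is not mentioned, neither included nor expressly barred.
- Analysis: the post value is missing and is handled by removal (section 2.15).

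Someone who attends a single class and then stops is within the stated follow-up group. The gap in section 2.4 is therefore limited to never-starters. People who were due a visit but do not return come under the removal rule as well.

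**2. Two readings of the removal rule.**
- *Missing values are removed.* The mixed model is fitted to everything observed, including baselines without a post value. Under likelihood estimation this is valid if missingness depends only on observed data, such as baseline and arm.
- *Incomplete participants are removed.* Baseline-only records are discarded. If loss depends on baseline, the pre and post means of completers no longer represent the randomised arm, although the data to adjust for this were collected.

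With two visits, baseline-only records add little precision to the time-by-group contrast. The difference between the readings is mainly one of validity.

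**3. How large could selection be?** The document gives no drop-out rate or pattern, so this is an assumption for scale only. If the worst fraction f of normally distributed outcomes in one arm were lost, that arm's mean would shift by φ(z_f)/(1 − f) standard deviations, where z_f is the standard normal quantile of f:
- f = 0.05: 0.109 SD
- f = 0.10: 0.195 SD
- f = 0.15: 0.274 SD

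These are upper ends, because loss is assumed to fall exactly on the worst outcomes. Loss of this kind depends on the unobserved value, so the mixed model alone would not repair it. Measuring the people concerned would.

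**4. The margin.** Inputs from section 2.5: matched pairs t-test, d = 0.5, significance level 0.05, minimum power 0.8. Sidedness is not stated.

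Power(n) = P(|T| > t(0.975, n − 1)), where T is noncentral t with n − 1 degrees of freedom and noncentrality d√n.

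The plan's figure reproduces. At n = 34 the noncentrality is 0.5 × √34 = 2.915 and two-sided power is 0.808; at n = 33 it is 0.795. A one-sided test would need 27. So 34 is the number of pre/post pairs with both arms pooled, shown as 17 per group.

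Margin: 36 − 34 = 2, and 2/36 = 5.6%.

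| Complete pairs | Pooled pre/post power |
|---|---|
| 36 | 0.831 |
| 34 | 0.808 |
| 33 | 0.795 |
| 32 | 0.782 |
| 30 | 0.754 |

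Chance of three or more losses among 36, for assumed independent loss rates:

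| Assumed loss | P(≥ 3 lost) | Enrolment for 34 completers, 34/(1 − loss) |
|---|---|---|
| 5% | 0.27 | 36 |
| 10% | 0.71 | 38 |
| 15% | 0.92 | 40 |

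**The case against.** The defence is substantial. Section 2.4 expressly keeps people who miss several sessions, so a reader who infers that only good attenders are assessed, and that the trial compares attenders with attenders, goes beyond the text. Removal of missing data without imputation is compatible with a mixed model fitted to all observed values. Analysis sets and sensitivity analyses are commonly left to a fuller document. Retention is taken seriously: conflicts are screened at eligibility, reminders cover the post-intervention visits, missed classes prompt contact, and two feasibility studies examined retention. This is also a pilot. Most of this stands. It narrows the point to the never-starter gap and the undefined rule, and it makes the timing of the incentive a matter of preference.

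Other stronger readings also fail. A reader might call the trial unmasked because participants know their arm, but section 2.7 masks the outcome assessors, except those who use instruments such as MRI. A reader might take the consent wording, "no penalty except possible removal from the study", as an exclusion rule for the analysis. It is general consent language, speaks only of a possibility, and does not say that declining one procedure removes a participant's data. Nor does unequal drop-out between arms bias the comparison by itself; the loss must be related to outcome. The document neither shows nor excludes that.

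On the margin, the 48 first planned also covered enrolment difficulties, so its excess of 14 over 34 was not purely an attrition allowance. Crossing the margin costs little power at first.

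What the objection does not remove is that section 2.15 makes an affirmative choice. One ordinary reading of that choice undermines the planned model, and the follow-up commitment stops short of everyone randomised.

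**Conclusion.** The point holds in a limited form. As written, a randomised never-starter has no stated post-intervention visit, and the removal rule can be read as deleting incomplete participants. If it is applied that way, the analysed sample is partly defined after randomisation and usable baselines are lost. This rests on two things the document leaves open: that never-starters are in fact not invited, and that removal applies to participants and not just to values. The direction and size of any bias cannot be established from the document.

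The arithmetic is firm but secondary. The statement that 36 still meets the minimum power holds only with at most two losses; a third takes pooled pre/post power to 0.795. That margin concerns the pooled test and says nothing about power for yoga versus exercise, which is a separate question. Fitting the model to all observed values would improve validity and would recover little power. The matter is worth correcting and is not fatal to the trial.

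**What to change.** 1. **Section 2.4.** State that every randomised participant is invited to the post-intervention visit, whatever their attendance and including those who attend no session.
2. **Section 2.15.** Replace the removal sentence with wording such as: *Participants are analysed in their assigned arm. All observed values enter a likelihood-based mixed effects model, and participants with incomplete data are not deleted. A simple sensitivity analysis examines how far the conclusions depend on the missing outcomes.* Imputation is still not needed.
3. **Optional, section 2.4.** Hand over the same incentives at the post-intervention visit instead of the last class, so that they reward the visit that supplies the post-intervention outcome data.
4. **Section 2.5.** Qualify the power statement: 36 meets the minimum only with no more than two losses.

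The cost is wording, a few extra assessment visits, incentives delivered up to two weeks later if item 3 is adopted, and an ethics board notification. Recruitment is described as ongoing, so the changes can still help participants not yet assessed.

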## Ethics and dissemination

3

### Research ethics approval

3.1

All study procedures have been reviewed and approved by the Institutional Review Board (IRB) within Colorado State University’s Research Integrity and Compliance Review Office. Protocol approval number: 1799.

### Protocol amendments

3.2

Initial IRB approval was provided in April 2021 for a feasibility study. Since then, the study PI has submitted a number of amendments to update study procedures and personnel to support completion of this pilot randomized control trial (RCT). Those procedures were approved in October 2022. The study PI will continue to inform the IRB of any changes to the study and request formal approval for any study amendments. If it highly unlikely that the PI will make any protocol changes that affect enrolled participants, however, if this occurs, participants will be informed of relevant study changes and re-consented, if necessary.

### Consent

3.3

Written informed consent is acquired by the study PI and Co-PI from participants or their legal power of attorney. This study includes two consent forms (see appendices) – one for the main study and one specific to MRI procedures (this is only acquired from participants who are eligible for MRI). Consent is acquired during a pre-intervention assessment visit, which occurs after participants are screened for eligibility. To note, if participants are deemed ineligible for the study during screening, the research team retains none of their information, with the exception of their initial email correspondence for recruitment tracking. Written informed consent procedures include the following steps: (1) Participants are emailed consent form(s) in advance of their pre-intervention assessment visit. (2) Upon arrival at the pre-intervention assessment visit, participants review a printed copy of the consent form(s) with the PI or Co-PI, who clarify procedures and answer questions. (3) After questions are addressed, participants initial and sign consent form(s) and the PI or Co-PI also signs the form(s). All participants are offered a copy of the signed consent form at this time. (4) Throughout the study, participants are reminded that they can decline to complete any procedures, which has no penalty except possible removal from the study.

### Confidentiality

3.4

Data confidentiality is maintained through steps outlined in the data management section. Additionally, participant confidentiality is maintained during research team member communication by only using initials or first names during electronic or verbal communication about participants, use of first names or initials on all study materials (e.g., polar watches include participant initials to avoid mix-ups), and use of secure communication when any sensitive information (e.g., participant phone numbers) are shared between team members.

### Access to data

3.5

The study PI and Co-PI will have direct access to the complete final dataset. Other research team members will be granted access to the complete dataset if they submit a request with scientific merit to the study PI. Otherwise, research team members with certain expertise (e.g., with ANS data analysis) will likely only have access to those specific data to prevent accidental disruption, deletion, or corruption of data files.

### Ancillary and post-trial care

3.6

Research team members are closely monitoring study outcomes (e.g., TBI-QOL measures) that may indicate participants need mental health support. The study team has prepared a list of local resources to share with participants in instances where mental health needs are identified. Provisions for compensation for those who suffer harm from trial participation are not available at this time, but they are unlikely to be needed, as prior studies have shown no adverse effects of yoga (and similar precautions are in place for exercise sessions).

### Dissemination policy

3.7

The research team plans to disseminate study findings via peer-reviewed publications, conference abstracts, and within grant proposals. The study PI is also responsible for providing yearly updates to the Boettcher Webb-Waring Biomedical Research Award Foundation; this report will briefly describe the study status and group-level outcomes, once available. Authorship for peer-reviewed manuscripts and conference abstracts will be determined following the International Committee of Medical Journal Editors guidelines, and authorship will be discussed in initial stages of manuscript preparation. Finally, the research team will share yoga and exercise protocols upon request. The team also plans to share de-identified participant data in a public repository; however, this is pending acquisition of funds to provide training and time for submission by a team member.

## Discussion

4

Individuals with chronic brain injury often experience poor balance and ANS dysfunction, which together can increase fall risk and reduce quality of life (McCulloch et al., 2010; Wilson et al., 2017; Perez et al., 2018; Khalid et al., 2019; Klima et al., 2019; Xiong and Leung, 2019). Here, we compare a group yoga intervention to a group low-impact exercise intervention and evaluate changes in balance and ANS function, along with the integrity of neural networks, task-dependent brain activity, cognition and quality of life. There is a growing body of literature on yoga for brain injury, but in prior work (Stephens et al., 2020), single-arm intervention designs were used. To determine if the positive outcomes observed after yoga are uniquely associated with yoga, this protocol introduces a comparable group exercise intervention in a pilot randomized control trial design. The benefits of exercise for acquired brain injury are well documented (An and Shaughnessy, 2011; van Duijnhoven et al., 2016) so we anticipate some degree of functional improvement in both groups. However, we also anticipate that the unique features of yoga may have a greater impact on certain functional outcomes.

### Expected results

4.1

#### Primary outcomes

4.1.1

Given our prior work (Schmid et al., 2012; Stephens et al., 2020), we expect significant improvements in balance as a result of the yoga intervention. However, we also expect that participants in the low-impact exercise group will experience improvements in balance. As such, we hypothesize significant within-subject differences in balance performance, but no between-group differences. We have different predictions for the ANS outcome. To-date, there is limited research investigating the effects of yoga on ANS function in populations with chronic acquired brain injury. Nevertheless, evidence from healthy adults indicate that yoga may improve ANS function (Zou et al., 2018). As such, we hypothesize that participants in the yoga group will have significantly greater improvements in ANS function than those in the low-impact experience group.

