**Methods:**

This study is a single-blind randomized controlled trial comparing group yoga to group low-impact exercise. Participants must be ≥18 years old with chronic ABI and moderate balance impairments. Group yoga and group exercise sessions occur twice a week for 1 h for 8 weeks. Sessions are led by trained adaptive exercise specialists. Primary outcomes are balance and ANS function. Secondary outcomes are brain function and structure, cognition, quality of life, and qualitative experiences. Data analysis for primary and most secondary outcomes will be completed with mixed effect statistical methods to evaluate the within-subject factor of time (i.e., pre vs. post intervention), the between-subject factor of group (yoga vs. low-impact exercise), and interaction effects. Deductive and inductive techniques will be used to analyze qualitative data.

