**Discussion:**

Due to its accessibility and holistic nature, yoga has significant potential for improving balance and ANS function, along with other capacities, in adults with chronic ABI. Because there are also known benefits of exercise and group interaction, this study compares yoga to a similar, group exercise intervention to explore if yoga has a unique benefit for adults with chronic ABI.

**Clinical trial registration:**ClinicalTrials.gov, NCT05793827. Registered on March 31, 2023.

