Specifically, our team is now conducting a single-blind pilot randomized control trial comparing two intervention arms: 8-weeks of group yoga and 8-weeks of low-impact group exercise in adults with chronic acquired brain injury. All prior studies (Grimm et al., 2017; Stephens et al., 2020, 2023) have been conducted as single-arm yoga intervention studies where participants served as their own controls, and baseline assessments were conducted before no-contact waiting periods and/or the intervention. Therefore, it is possible that the positive outcomes we have reported could be exclusively attributed to well-established benefits of physical exercise or social interaction. In order to determine if yoga has a distinctive impact on functional outcomes, like balance and ANS function, it is necessary to include a control group that mirrors many of the features of the yoga intervention, but lacks unique features of yoga (e.g., breath-to-movement connection). Thus, adding a low-impact group exercise control (Leach et al., 2023) is an essential next step to evaluate if yoga has a unique benefit for adults with chronic ABI. Again, our primary outcome measures are designed to evaluate balance performance and heart rate variability (HRV), as an indicator of ANS function. Secondary outcome measures are designed to: (1) measure neural underpinnings of functional improvements, specifically - functional and structural connectivity of neural networks and task-dependent neural activation during balance tasks and (2) evaluate previously observed outcomes of cognition, quality of life, and qualitative experiences. The overarching purpose of this manuscript is to describe, in detail, all components of our trial protocol to support transparency and replication of methods.

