#### Balance data

2.13.1

T-Scores from the NIH Toolbox Standing Balance Task and center of pressure metrics from the force plate will use mixed effects statistical model to assess prospective within-subject (factor of time) and between-group (yoga vs. control) differences in balance performance.

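### The balance hypothesis predicts no group difference, but the article plans only difference tests with no margin, and about 18 per arm cannot tell similar arms from arms a medium effect apart

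*Protocol article*

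**What the plan says.** Section 4.1.1 (Expected results, Primary outcomes) expects balance to improve in both arms and concludes: "we hypothesize significant within-subject differences in balance performance, but no between-group differences". The same paragraph describes the expected gain as resulting from the yoga programme. For ANS function it makes a directional prediction in favour of yoga.

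Section 2.13.1 (Balance data) plans a "mixed effects statistical model to assess prospective within-subject (factor of time) and between-group (yoga vs. control) differences in balance performance". The abstract's Methods adds "the between-subject factor of group (yoga vs. low-impact exercise), and interaction effects". Neither place gives an equivalence margin or an interval criterion.

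Section 2.5 (Sample size) states "Power was determined by focusing on the primary outcome of balance", using a "matched pairs t-test with a medium effect size" (d = 0.5), "a minimum power of 0.8 and a significance level of 0.05". It arrives at 17 per group (34 in total) and says that the revised enrolment of 36 still meets the minimum power. Allocation is 1:1 (section 2.6), so 36 means about 18 per arm.

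Both arms are active. The abstract's Discussion gives the purpose of the comparison as "to explore if yoga has a unique benefit for adults with chronic ABI".

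**The concern.** A prediction of no difference cannot be supported by failing to find one unless the trial is precise enough to exclude differences that matter. The article states the prediction and names only difference tests, so the text leaves non-significance as the sole available support. The ANS hypothesis does not have this problem, because a directional claim suits a difference test.

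The other half of the hypothesis is a change over time. With no untreated arm, that change mixes any programme effect with practice on the repeated tests, possible regression to the mean (entry requires self-reported balance impairment of at least moderate degree, section 2.2) and concurrent care or exercise, which section 2.8.3 permits.

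At stake is a primary conclusion that both programmes improve balance and that yoga is no different, resting on a result too imprecise to show either part.

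**Working it through.** **Inputs.** From the article: 36 participants, 1:1, so n = 18 per arm; d = 0.5; alpha 0.05 (sidedness not stated, two-sided taken); power 0.80. Assumed, because the article does not give them: a pre-post correlation r = 0.7 where baseline adjustment is used, normal data, and the equivalence margins shown. Results are in SD units.

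**1. The article's own figure.** A paired t-test with d = 0.5 and two-sided 0.05 has noncentrality 0.5·√n. Power is 0.795 at n = 33 and 0.808 at n = 34. So 34 reproduces as the total number of pre-post pairs, both arms together. One arm of 17 pairs has power 0.49. The stated size therefore covers the pre-post change across all participants, not the randomised contrast.

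**2. Between-arm test, 18 per arm.** Noncentrality d·√(n/2), df = 34.
- True difference 0.5 SD of change: 0.5·√9 = 1.5, power 0.31, so a miss in 69% of trials.
- If 0.5 SD is in raw-score units and the test is baseline-adjusted with r = 0.7, the effective d = 0.5/√(1 − 0.49) = 0.70, power 0.53, so a miss in 47%.

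**3. Precision.** 95% CI half-width = t(0.975, 34)·√(2/18) = 2.032/3 = 0.68 SD. Baseline-adjusted: 0.677·√0.51 = 0.48 SD.

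**4. The full predicted pattern.** This is a simulation of change scores with SD 1 and 18 per arm. The pattern is a significant improvement over time across all participants together with a non-significant group-by-time interaction.

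| Mean change, one arm / other arm | True difference | Pattern occurs |
|---|---|---|
| 0.5 / 0.5 | 0 | 79% |
| 0.25 / 0.75 | 0.5 | 57% |
| 0.5 / 1.0 | 0.5 | 69% |
| 0 / 0.5 | 0.5 | 21% |
| 0.1 / 0.9 | 0.8 | 29% |
| 0.5 / 1.3 | 0.8 | 35% |
| 0 / 1.0 | 1.0 | 14% |
| 0 / 0, no retest drift | 0 | about 2% |

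The figures are the same whichever arm does better.

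**5. Could the design show similarity formally?** Two one-sided 5% tests, arms truly identical, 18 per arm. The 90% CI half-width is about t(0.95, 34)·√(2/18) = 1.691/3 = 0.56 SD, already wider than a ±0.5 SD margin.
- Assumed margin ±0.5 SD: power about 2%. Baseline-adjusted with r = 0.7, about 32%.
- Assumed margin ±0.8 SD: about 52%.
- Assumed margin ±1.0 SD: about 80%.

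**6. Direction of further error.** Incomplete data are removed (section 2.15), and only participants who reach the fifth Toolbox task go on to the force plate (section 2.9.1.1). The analysed numbers can therefore be lower than 18 per arm.

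**The case against.** The sentence stands under expected results and is a prediction. A reader might infer a rule by which non-significance confirms it, but the article states no such rule. What remains is that it also offers no other criterion.

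A reader might also infer that the Introduction criticises the earlier single-arm studies for the very lack described here. It does not. Its worry is that "it is possible that the positive outcomes we have reported could be exclusively attributed to well-established benefits of physical exercise or social interaction", and the exercise arm answers that worry. It mentions neither retest practice nor regression to the mean. Regression to the mean is itself only possible: entry uses a self-report item while the outcome is instrumented sway, and the article does not give the link between them.

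It is also tempting to say that the pattern would be likely when one arm is clearly better, or when neither works. The table does not support this. At differences of 0.8 to 1.0 SD the pattern occurs in 14–35% of trials, and with no change in either arm and no drift in about 2%.

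Finally, this is a pilot, and a margin could sit in an analysis plan that is not shown. The pilot label excuses low power, but it does not turn a non-significant difference into evidence of similarity. The point rests on the hypothesis and analysis as printed, not on the missing detail.

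**Conclusion.** The point holds for medium differences. As printed, the balance hypothesis can be supported only by a non-significant test, and with 18 per arm the predicted pattern separates poorly between equal arms (79%) and arms 0.5 SD apart that both improve (57–69%). Similarity could be shown with reasonable power only at a margin near 1.0 SD.

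The probabilities depend on the unit of the 0.5 SD difference, on the assumed correlation and on the size of the true difference. The power to show similarity also depends on the assumed margin.

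Separately, the pre-post change is uncontrolled, so the causal wording about yoga in section 4.1.1 is not supported. The randomised contrast can attribute a difference between the programmes, but that is the comparison the trial was not sized for.

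**What to change.** In sections 2.13.1 and 4.1.1:
- Replace the prediction of no difference with an estimation statement. The main balance result is the baseline-adjusted yoga-minus-exercise difference in Toolbox Standing Balance T-score, with its 95% CI.
- Claim similarity only if the 90% CI lies wholly within a margin that the team chooses, justifies and fixes before unmasking. If the 95% CI includes zero and the similarity criterion is not met, report the comparison as inconclusive.
- Describe within-arm changes as uncontrolled, and remove wording that attributes them to yoga.

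The cost is wording plus the choice of a margin; no change to recruitment, visits or data collection is needed. The drawback is that the balance conclusion will probably read as inconclusive, which is what a trial of this size can usually support.
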